*Enrolment in the sub-study and collection of baseline data:* Out of all the LBW infants enrolled in the main trial, a sub-sample of the LBW infants aged >72 hours to 7 days and their mothers will be included in this sub-study. Among the subjects enrolled in the main trial in a day, 4-6 subjects will be selected randomly per day and approached by the supervisor on Day 4 for obtaining additional consent for the sub-study. In case of non-consent, the subsequent mother-infant dyad will be approached. Data will be recorded to keep track of mothers who consented and did not provide consent. In these women, additional samples or information will be collected for the sub-study. Baseline information will be collected for the sub-study to describe the study sample and to adjust for any confounding. These variables include sociodemographic details (age, years of schooling of the mother, wealth index, total family income, family type, religion and working status of mother), reported gestational age, birth order, place and mode of delivery, birth weight of the baby, previous breastfeeding experience, maternal dietary habits, iron and calcium tablet intake, history of maternal post-partum illnesses (fever). Maternal anthropometry (height and weight) will also be done at enrolment to ascertain baseline nutritional status.

*Informed Consent:* Written individual informed consent for this sub-study will be obtained from the caregivers at enrolment, from whom additional samples and information will be collected. The informed consent form for the sub-study has been translated into simple Hindi language that can be easily read and understood. The purpose of the study, procedures to be performed, samples to be collected and stored will be explained in detail. In those who are unable to read, the worker who obtains consent will read out the consent form. The mothers' understanding of the information will be confirmed. In those who are unable to sign, a thumb imprint will be taken which will be witnessed (counter signed) by an impartial literate witness. Only the eligible LBW babies, whose parents provide informed consent will be enrolled for this study.

*Outcome ascertainment:* Outcomes specific to the sub-study will be measured by a independent team trained in the study related measurements and laboratory procedures in the study subjects enrolled through home visitations. There will be a total of 4-5 such teams. Each team comprises

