infant breast milk intake, gut inflammation, multivariable linear regression models will be used. Covariates identified as potential confounders will be included in the regression models for adjustment. Regression analysis will also be done to examine the effect of infant milk intake, postpartum depressive symptoms and gut inflammation on linear growth velocity (birth to 3 months and 3 to 6 months) and LAZ scores of the LBW infants. To assess dose-response relationships between duration of KMC and volume of breast milk output generalized additive models shall be used. We may also use Instrumental Variable analyses to study associations between actual intensity of SSC and Breast feeding and the outcomes of the proposed studies.

For qualitative outcomes e.g. mothers with PHQ9 score  $\geq 10$ , lactation failure, perceived milk insufficiency, proportions will be reported. If necessary to adjust for any baseline differences, univariable and multivariable logistic regression analysis or analyses with generalized linear models of the binomial family with a log link shall be done to estimate the impact of KMC on these outcomes. Potential interaction between cKMC and all other variables on the outcome measures will be examined by including interaction terms in the multivariable regression models, after identifying subgroup differences by simple stratified analyses. In order to quantify biologic interactions(52) we will estimate the relative excess risk due to interaction(RERI) with its 95% CI(53, 54).

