**Plan of Analysis**

The analysis will be done using STATA version 14 (Stata Corporation, College Station, TX). All analysis will be performed on intent to treat basis.

Group wise comparison will be done for distribution of baseline features such as

- household characteristics (wealth quintile, religion, caste, type of family, number of family members)
- maternal and paternal characteristics (mother's age, mother's education, maternal occupation, father's age, father's education and occupation)
- birth related characteristics (place and type of delivery, birth order, parity) and
- infant characteristics (sex, birth weight, gestational age)

Proportion who initiated breastfeeding within 1 hour, exclusive breastfeeding, hospitalizations (at the 1 month visit) will also be presented by group.

Gestational age will be calculated from ultrasonography (USG) report, hospital records or maternal recall, whichever available, in the given order of preference. Proportion of women with available antenatal USG will be reported.

The distribution of the continuous outcomes such as (maternal salivary cortisol concentration, PHQ-9 scores) will be examined by using histogram and normal probability plot. Skewness and kurtosis coefficient will be measured. If skewness coefficient tends to zero and kurtosis coefficient tends to 3, distribution will be normal. For normal distribution, mean and standard deviation (SD) will be reported for quantitative variables. Median and interquartile range (IQR) will be reported for non-normal distribution. For non-normal continuous outcomes appropriate transformation (log or others) will be done before applying the tests of association or we will use non-parametric tests such as Wilcoxon rank-sum test will be performed for comparison between study arms.

The proportion of minimal, mild and moderate to severe depressive symptoms as defined by the PHQ-9 scores will be presented by group.

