**Effect of community-initiated KMC on maternal postpartum depressive symptoms and stress - a randomized controlled trial**

To examine effect of ciKMC on maternal moderate to severe depressive symptoms multivariable logistic regression analysis or analyses with generalized linear models of the binomial family with a log link shall be done. Additionally, multinomial logistic regression analysis will be done to examine effect of ciKMC on prevalence of categories of maternal depressive symptoms viz. minimal (reference group), mild, and moderate to severe depressive symptoms.

For estimating effect of ciKMC on continuous outcomes i.e. maternal salivary cortisol concentration and mean PHQ-9 scores multivariable linear regression will be done if distribution is normal. If distributions are skewed, appropriate transformation (log or others) will be done before conducting linear regression. Alternatively, we will use non-parametric tests such as Wilcoxon rank-sum test for comparison of these outcomes between study arms.

For all the analyses, univariable regression analysis will be done as an initial step to assess the effect of ciKMC on the outcomes considered. This will be followed by multivariable regression analysis after including potential confounding variables in the model, defined as variables which are unequally distributed between the two groups (relative difference of >10%).

Potential interaction between KMC and other variables will be examined by including interaction terms in the multivariable regression models. Stratified analysis will be presented and any biologic interaction will be estimated with the relative excess risk due to interaction (RERI).

Planned Sub-group analysis:

- 1) By preterm vs. term birth
- 2) Birth weight +/- 2 kg if it does not substantially correlate with term vs. preterm birth.

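### Interaction tests are open-ended beyond the SAP's two planned subgroups, with no limit on their number, no adjustment and no exploratory label

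*Combined protocol and SAP*

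**What the plan says.** **Protocol** (Description of the PhD sub-study, data analysis). "Potential interaction between cKMC and all other variables on the outcome measures will be examined by including interaction terms". The terms go into the multivariable models "after identifying subgroup differences by simple stratified analyses". RERI with its 95% CI is then estimated to quantify biologic interaction. The sentence is not tied to one outcome, so it covers milk intake, cortisol and the gut markers as well as PHQ-9.

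**SAP** (depressive symptoms and stress, Plan of Analysis). "Potential interaction between KMC and other variables will be examined by including interaction terms in the multivariable regression models". Stratified results are to be shown and RERI estimated. Two planned subgroup analyses follow. The first is "By preterm vs. term birth". The second is birth weight around 2 kg, kept "if it does not substantially correlate with term vs. preterm birth".

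The SAP therefore no longer says that every variable is a candidate, and it no longer contains the stratify-first step. It does not withdraw the protocol's rule, and it does not confine interaction testing to its two subgroups. Neither document gives a number of interaction tests, a significance level for them, a multiplicity rule, or a statement that those outside the planned subgroups are exploratory.

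**The concern.** An interaction p-value means what it says only if the reader knows how many were examined. Under the protocol's rule the analyst looks at strata for every variable, picks those that seem to differ and tests those. A paper that follows the rule could show one interaction test with p below 0.05 and give no sign that many strata had been inspected. The SAP's two named subgroups do not cure this while an open search is allowed beside them.

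The trial was also sized for main effects only. A real interaction would often be missed, and a chance one could appear with RERI attached, under the plan's own term of biologic interaction and with no caveat. What is at stake is how effect-modification results are read. The overall estimate of the effect of ciKMC is untouched.

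**Working it through.** **Inputs**
- PHQ-9 ≥10: control 0.19, KMC 0.133, alpha 5%, power 90%, 874 per arm, 975 per arm with about 10% attrition (protocol, Annexure 3; SAP, Sample Size).
- Candidate variables: the SAP's baseline list, counted as 5 household + 6 parental + 4 birth-related + 3 infant = 18. The protocol's own baseline list gives 18, or 19 if iron and calcium are counted separately.
- Significance level per interaction test: not stated; 0.05 is an assumption.

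**1. The plan's own figure.** Two proportions, pooled variance, two-sided, mean rate 0.1615:

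n = [1.96·√(2 × 0.1615 × 0.8385) + 1.2816·√(0.19 × 0.81 + 0.133 × 0.867)]² / 0.057² = 874 per arm.

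This matches. 874/0.90 = 972, close to the stated 975. The sizing covers the main effect only.

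**2. False interactions, independent tests.** P(at least one) = 1 − (1 − α)^k.

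| Tests k | α = 0.05 |
|---|---|
| 2 (planned subgroups) | 9.8% |
| 7 | 30% |
| 13 | 49% |
| 14 | 51% |
| 18 (SAP list) | 60% |
| 19 | 62% |

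For k = 18, the result is 17% at α = 0.01 and 85% at α = 0.10.

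The expected number of false interactions on PHQ-9 ≥10 is 18 × 0.05 = 0.9. Over the SAP's five outcomes it is 18 × 5 × 0.05 = 4.5. Expected counts do not depend on independence.

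**3. Allowing for correlation.** Simulation of 3,000 trials per setting, with 1,756 mothers (1,950 less about 10%), rates 0.19 and 0.133, 18 binary covariates split 50:50, no true interaction on the odds-ratio scale, and Wald tests at 0.05:

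| Covariates | At least one false interaction |
|---|---|
| Independent | 58% |
| Latent correlation 0.3 | 56% |
| 0.3 plus three near-duplicate pairs | 52% |
| 0.5 plus three near-duplicate pairs | 45% |

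Two tests gave 9–10% throughout.

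**4. Role of the screen.** Testing only the covariate with the largest stratified difference gave the same rates as testing all 18. The inflation comes from the number of variables looked at. The screen neither adds to it nor protects against it, but it hides the number.

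**5. Power for a true interaction.** A main effect with 90% power has expected z = 1.96 + 1.28 = 3.24. In a 50:50 subgroup each half-sample effect has √2 times the main-effect standard error, so their difference has twice that error. For an interaction as large as the main effect, z = 3.24/2 = 1.62 and power = 1 − Φ(1.96 − 1.62) = 1 − Φ(0.34) = 0.37. An uneven split gives less.

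**The case against.** Five points can be made for the plan.

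- *The SAP has moved on.* It is the specific plan for the PHQ-9 outcome, it drops the stratify-first step, and it names two subgroups. A reader might infer that the SAP repeats the protocol's rule; it does not. This stands in part. The SAP still admits unnamed further variables with no limit, and it leaves the protocol's wording in force for the other outcomes.
- *The number of tests is unknown.* The 18 variables are listed for baseline comparison, not as effect modifiers. The SAP places interaction terms in multivariable models whose covariates are those more than 10% unequal between arms, which may be far fewer. Several overlap, such as parity with birth order. This stands. A reader might conclude that a false interaction is more likely than not, but that needs at least 14 effectively independent tests at 0.05, and the documents fix neither number.
- *The screen is not the cause.* This stands; step 4 shows that the number of looks drives the error rate.
- *A nominal p-value is not a subgroup claim.* This also stands. Neither document says that a nominally significant interaction will be declared a finding. The fault is that nothing marks it as exploratory.
- *The birth-weight condition is harmless.* A reader might see it as another data-driven choice that distorts the tests. It depends on the correlation between two baseline variables, not on outcomes or treatment effects, so it does not inflate type I error. Nor does the SAP rest gestational age chiefly on recall: ultrasound comes first, hospital records second and recall last.

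**Conclusion.** The concern holds in a limited form. The protocol states an unrestricted interaction search with selection on stratified results. The SAP narrows this but leaves it open-ended. With no limit, adjustment or exploratory label, interaction p-values outside the two planned subgroups should not be read at face value.

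The size is conditional. If all 18 listed variables were tested at 0.05 on PHQ-9 ≥10, the chance of at least one false interaction is about 60% under independence and about 45–60% allowing for correlation, against about 10% for the two planned subgroups. Fewer tests or a stricter level would lower it. Power of about 37% assumes equal subgroups and an interaction as large as the planned main effect.

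The documents do not support an unconditional statement that a false subgroup finding is more likely than not, or that one will be claimed. This is a matter of secondary analysis and reporting, worth correcting because the correction is nearly free.

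**What to change.** - Protocol, data analysis: delete the step that selects interactions from stratified results, and the reference to every other variable.
- SAP, primary outcome (PHQ-9 ≥10): limit formal interaction tests and RERI to the two planned subgroups, preterm versus term and birth weight around 2 kg. State the significance level. Two tests at 0.05 carry 9.8%; two at 0.025 carry 1 − 0.975² = 4.9%.
- Any other interaction or stratified result, for this and the other outcomes in both documents: present as exploratory, with estimates and confidence intervals, no significance claims, and the number of variables and outcomes examined.
- Optional: remove the birth-weight correlation condition so that both subgroups are always reported. It is not needed for error control.

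The cost is a few sentences in each document and somewhat less analysis. The downside is fewer exploratory tests; exploratory estimates can still be shown.

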## **Role and Responsibility of all Participating Institutions**

The partner Institutes are St. John's Medical College, Bangalore, which is one of the leaders in Nutrition Biochemistry in India and THSTI, which is an innovative institute leading research in Biotechnology. [name] of St. Johns Medical College who will be a co-investigator of this research project, will help in training study team for  $^2\text{H}_2\text{O}$  administration, saliva collection techniques and Lab analysis of Saliva samples for estimating Infant milk intake (breast milk output). [name] of THSTI who will be another co-investigator in this project will help in Lab analysis for Gut microbiome at THSTI lab.

## **Ethics**

Ethics clearances have been obtained from the institutional Ethics Committee of the Society for Applied Studies for this sub study. The ethical approval will be provided to the Regional Committees for Medical and Health related Ethics (<https://www.etikkom.no/rek>) in Norway for information and additional comments (if any). We have a Memorandum of Understanding (MoU)

with National Health Mission (NHM) in Haryana and approval to do community based studies in partnership with the local government.

## Sources of Funding

The study (PhD proposal) is partly supported (500,000 NOK) by the Centre for Intervention Science in Maternal and Child Health (CISMAC; project number 223269), which is funded by the Research Council of Norway through its Centres of Excellence scheme and the University of Bergen (UiB), Norway. This support will be used for analysis of infant breast milk intake using deuterium oxide method.

The research proposal has also been submitted to Department of Biotechnology, Government of India for additional funds required for the other objectives. A decision is awaited. The Society for Applied Studies, New Delhi (SAS) will contribute by enabling the PhD objectives to be pursued within the context of the trial and any shortfall in funds to complete the primary objectives for the PhD will be supported by SAS through institutional overheads.

## Time frame

| S/N | Activity                                                                                              | Timelines        |
|-----|-------------------------------------------------------------------------------------------------------|------------------|
| 1   | Recruitment of staff, training and standardization of study workers, development of study instruments | 1 month          |
| 2   | Enrolment of subjects with ongoing biological sample collection                                       | 8 months         |
| 3   | Follow up and completion of sample collection, anthropometry measurements and lab analysis of samples | 6 months         |
| 4   | Data cleaning and analysis                                                                            | 6 months         |
| 5   | Paper writing (3 papers)                                                                              | 9 months         |
| 6   | Total duration                                                                                 | 30 months |

## Annexures

### Annexure 1. Conceptual framework: Kangaroo mother care – possible biological mechanisms

[figure not shown]

## Annexure 2. Implementation strategy for the sub-study

[figure not shown]

### Annexure 3. Sample Sizes

## Infant Breast Milk intake

#### Sample Size considerations

|                                                                                                          |            |
|----------------------------------------------------------------------------------------------------------|------------|
| Standard deviation of breast milk intake in control group at around day 14 (ml/d)                        | 200        |
| Expected increase in Mean (ml/d) in Breast milk output (~10%)
[Mean milk output at 0-1 month: 600 ml] | 60         |
| Effect size (SD)                                                                                         | 0.3        |
| Alpha error (%)                                                                                          | 5          |
| Power (1- beta) %                                                                                        | 90         |
| Required sample size per group                                                                           | 234        |
| Total sample size required                                                                        | 468 |
| TOTAL SAMPLE SIZE APPROVED FOR THIS OUTCOME (including 15% attrition)                             | 550 |

Ref: Teresa H. M. da Costa et al. How Much Human Milk Do Infants Consume? Data from 12 Countries Using a Standardized Stable Isotope Methodology. *J. Nutr.* 140: 2227–32, 2010

9/3/2017

8

## Maternal Postpartum Depressive symptoms (PHQ 9 $\geq 10$ )

#### Sample Size considerations

|                                                                                        |             |
|----------------------------------------------------------------------------------------|-------------|
| Proportion of PP depression in control group                                           | 0.19        |
| Expected proportion of PP depression in KMC group
(expected 30% relative reduction) | 0.133       |
| Estimated risk difference                                                              | 0.057       |
| Power (1- beta) %                                                                      | 90          |
| Alpha error (%)                                                                        | 5           |
| Required sample size for each arm                                                      | 874         |
| TOTAL SAMPLE SIZE FOR EACH ARM (including ~10% attrition)                       | 975  |
| TOTAL SAMPLE SIZE (including ~10% attrition)                                    | 1950 |

Ref: Gelaye B, Rondon MB, Araya R, Williams MA. Epidemiology of maternal depression, risk factors, and child outcomes in low-income and middle-income countries. *Lancet Psychiatry* 2016;3: 973–82

# Stress (Salivary cortisol levels)

## Sample Size considerations

|                                                                                               |            |
|-----------------------------------------------------------------------------------------------|------------|
| Standard deviation of Cortisol in control mothers(ug /dl)                                     | 5          |
| Expected Mean difference (ug/dl) in Cortisol levels(~20%)
[mean in control mothers 7ug/dl] | 1.5        |
| Effect size (SD)                                                                              | 0.3        |
| Alpha error (%)                                                                               | 5          |
| Power (1- beta) %                                                                             | 90         |
| Required sample size per group                                                                | 234        |
| Total sample size required                                                                    | 468        |
| TOTAL SAMPLE SIZE APPROVED FOR THE STUDY (including attrition)                         | 550 |

Ref: Morelius E, Ortenstrand A, Theodorsson E, Frostell A. A randomised trial of continuous skin-to skin contact after preterm birth and the effects on salivary cortisol, parental stress, depression, and breastfeeding. Early human development. 2015;91(1):63-70.

9/3/2017

24

